## Abstract

**Background:**

Stepfamilies are a prevalent family form. However, less stable than nuclear, first marriage families due to the presence of risk factors such as the absence of social norms and the presence of stepchildren. Stepfamilies have unique educational needs regarding stepparenting and co-parenting issues. The development and documentation of psychoeducational intervention strategies can facilitate dissemination of ongoing studies and promote transparency. This article describes the background, design and protocol of a randomized controlled trial (RCT) evaluating the eficacy and feasibility of a web-based Psychoeducational Simulation Game (*GSteps*). Behavior-modeling video training (BMT) is used to demonstrate and promote relational skills, stepparenting and co-parenting effective strategies for adults in stepfamilies. A mental health professional will be available within the *GSteps* platform for clarification or emotional support.

**Methods/design:**

A RCT design is presented to evaluate the outcomes of a self-administered, interactive and web-based psychoeducational Game targeting dyadic marital adjustment and interpersonal skills as the primary outcomes and remarriage beliefs, family function and stepparenting and co-parenting attitudes as the secondary outcomes. Other outcome measures include satisfaction with *GSteps*, participants’ knowledge learned after the intervention and a purposive sampling method will be used to access feasibility. The minimum required sample size is 112 participants (56 per condition) randomly allocated either to an experimental group (EG), receiving *GSteps* intervention, or to a wait-list control group (CG). A survey is conducted electronically. Assessments take place at baseline (*T_0_*), after the intervention (*T_1_*) and 1-month follow-up (*T_2_*).

**Discussion:**

This protocol presents a RCT aimed at evaluating the efficacy of a web-based psychoeducational intervention (*GSteps*) designed for improving marital, stepparenting and co-parenting skills in adults who live in stepfamilies. The use of the protocol and results of intervention studies may guide the use and refinement of web-based psychoeducational intervention for stepfamilies. Additionally, *GSteps* may become a tool for health professionals to enhance stepfamily functioning, stepparenting skills, and marital adjustment of remarried adults.

## Introduction

### Background

Remarriage has been characterized as a *phenomenon* since the 1960s (Schlesinger, 1968). Although the rate of remarriages has been declining steadily in recent decades for both men and women (Schweizer, 2019), cohabitation has become an increasingly common lifestyle choice. A growing proportion of cohabiting unions are second unions that form stepfamilies when there are stepchildren (Manning, 2015). Between 2007 and 2016, the rate of unmarried stepcouples in cohabitation increased by 29% (Stepler, 2017). This trend has been observed both in America and in European countries (Higgins et al., 2020), reflecting the increasing social acceptability of unmarried couples and families (Guzzo, 2018).

Although the literature identifies differences between remarried unions and cohabiting unions (e.g., Brown, 2006), both are less stable than nuclear, first marriage families (Cherlin, 2017). This instability has been explained by the absence of social norms about the functioning of families with stepchildren (Nock, 1995; Kelly and Ganong, 2011; Coleman et al., 2022). Nuclear families have socially prescribed norms and expectations (e.g., the parent role is clear within any biological family) that “institutionalizes” their family form. The absence of social norms, the ambiguity of roles and functions of stepfamily members (remarried and cohabiting) means that these families are not completely institutionalized (Cherlin, 1978) and contribute to a negative impact on stepfamily dynamics and marital relationship (Garneau and Pasley, 2017).

Other factors can also contribute to the instability of stepfamilies. For example, stepcouples have to simultaneously deal with the tasks related to couple formation and parenting, often with children in different developmental stages (Dupuis, 2007). Although much has been investigated about the intertwinement between stepcouples’ functioning and stepfamily functioning (e.g., Papernow, 2013), intervention programs designed for stepcouples are relatively scarce (Adler-Baeder and Higginbotham, 2004). Those available are mostly focused on stepparenting issues and use traditional education formats, with a facilitator moderating multiple group sessions (Nicholson et al., 2007).

Effective interventions to enhance stepcouples’ dynamics should address not only factors that are unique to stepparenting, but also factors that are inherent to the couple dyad (Halford et al., 2003; Adler-Baeder and Higginbotham, 2004). In common with other couple types, couples in stepfamilies may consider programs that promote general relationship skills such as communication training (e.g., Ahrari et al., 2020), problem-solving (e.g., Babcock et al., 2013), empathy skills (e.g., Adler-Baeder, 2007), conflict and stress management and building friendship and affection (Gottman, 1999). But for educational programs targeting stepcouples, it is important to consider their unique challenges. First, remarried people often face unrealistic thoughts around the notion that “the new partner should be perfect and better than previous one” (Higginbotham and Adler-Baeder, 2008a). Second, it is frequent to carry unresolved emotional patterns from previous marriage(s) to remarriage, such as feelings of guilty, betrayal or loss (Fredericson and Handlon, 1994; Faber, 2004). Third, after a previous marital dissolution, remarried partners feel social pressure to succeed (Fredericson and Handlon, 1994; Bernstein, 2000). Fourth, besides social pressure, the social network has to be rebuilt and there is a tendency to perceive lower levels of social support (Bradbury et al., 2000; Ganong and Coleman, 2017; Dainton, 2019). Fifth, the management of financial resources can be connected to, or dependent on, the economic decisions of former partners (e.g., complying with child support; Ganong and Coleman, 2017).

The interaction between parenting, co-parenting and stepparenting (with potential spillover effects in the quality of the relationship) should be considered when designing a program for stepcouples. Previous research has shown that the presence of unrealistic myths or expectations (e.g., “instant love” between stepparent and stepchild; Higginbotham and Agee, 2013; Santos et al., 2022), may strain stepfamilies. Overall, these myths are based on nuclear family ideology, where love is usually an automatic and unquestioned feeling (Ganong and Coleman, 2017). On the other hand, the myth that stepparents and stepchildren can never learn to love each other can lead to other difficulties in building a positive relationship (Coleman et al., 1994; Ganong and Coleman, 2017).

Difficulties in roles definition and early imposition of discipline actions in the stepchild’s rearing can also contribute to unhealthy relationships (Papernow, 1993; Adler-Baeder, 2007). Thus, to develop a healthy stepparenting, it is recommended that couples (1) developing realistic expectations (Fine and Kurdek, 1994; Higginbotham and Adler-Baeder, 2008b); (2) empathize by validating stepchildren’s feelings and emotions (Adler-Baeder, 2007; Agulhas and Anciães, 2018); (3) discuss with partner about stepparent role (Adler-Baeder, 2007; Papernow, 2013); (4) engage in cooperative parenting instead of trying to “replace” the non-residential parent (Adler-Baeder, 2007; Dupuis, 2007; Papernow, 2013); (5) recognize that the ex-spouse will always be part of stepfamily (Papernow, 2013); (6) utilize healthy co-parenting practices between ex-spouses protecting children from the details of divorce process (Pringle and Ehrenberg, 2005; Adler-Baeder, 2007; Pringle, 2008), parental conflict and loyalty conflicts (Papernow, 1993; Adler-Baeder, 2007; Agulhas and Anciães, 2018). These practices minimize children’s rejection behaviors; enhance positive stepfamily functioning; promote the construction of a unique stepfamily identity through the emotional connection of stepfamily members and increase marital quality and satisfaction (Papernow, 1993; Adler-Baeder and Higginbotham, 2004; Adler-Baeder, 2007; Gelatt et al., 2010).

### Developing a theory-based online educational game for promoting relational skills in stepcouples

Some non-traditional efforts have piloted ways to help stepcouples prevent marital and family difficulties (e.g., online intervention; telehealth; Braithwaite and Fincham, 2009; Gelatt et al., 2010). Web-based self-administered interventions with a behavior-modeling training (BMT) approach (i.e., visual demonstrations of behaviors) appear to increase self-efficacy and motivation (Cairncross and Mannion, 2001). BMT promote preparation for practice by visualizing the performance of certain behavior (Taylor et al., 2005). This approach is based on Bandura and Walters’ social-learning theory and has been shown to be effective in producing sustainable skill improvement and behavior change with video modelling in parenting intervention programs (Glang et al., 2007). According to that theory, human thought and behavior are influenced not only by real experience but also by direct observation. Bandura and Walters (1977) also concluded that learning is most effective when people observe the consequences of engaging in a specific behavior. Combined with interactive teaching aids, BMT allows individuals to access to learning environments to ‘practice’ problem-solving skills and critical thinking in a virtual simulation that replicates real-life problematic situations (Homanova et al., 2019). Additionally, there is evidence that self-administrated web-based programs can be more effective than face-to-face group sessions (U.S. Department of Education, 2009). Taylor et al. (2005) conducted a meta-analysis of 117 studies of adult training programs and concluded that BMT was effective in producing sustainable skill improvement and post-training behavior change. Attempts to include technology’ advances to differentiate the training modalities have been increasing, especially due to the pandemic situation, but randomized controlled trial (RCT) studies that investigate stepfamily outcomes remain limited (Gelatt et al., 2010).

Prevention and psychoeducational programs for stepfamilies generally provided positive effects (Whitton et al., 2008). A meta-analysis of 14 studies conducted by Lucier-Greer and Adler-Baeder (2012) concluded that education programs for stepcouples had large effects in parenting and family functioning. *Smart Steps Program* (Higginbotham and Adler-Baeder, 2008b) was one of the education programs evaluated by these authors. They concluded that *Smart Steps* increased relationship skills, stability, and commitment for stepparents and these improvements endured 1 month after the study. Clinical programs for stepfamilies have also shown similar positive results. Behavioral family intervention (Nicholson and Sanders, 1999) or emotionally focused family therapy (Furrow and Palmer, 2007) were two different interventional approaches that demonstrated greater reductions in couple conflict over parenting practices and promote stability, cohesion and attachment in the developing stepfamily system.

The web-based, interactive training programs for couples in stepfamilies (e.g., Parent et al., 2019), in particular those using BMT (Trone, 2002; Gelatt et al., 2010) have also demonstrated promising results. Specifically, Trone (2002) reported higher levels of family adjustment in families with a stepfather after the intervention. Gelatt et al. (2010) documented significant effects in stepparenting, stepfamily, and couple domains, with both parents and stepparents increasing their skills. However, these benefits should be interpreted with caution as several limitations were noted, including the lack of random assignment, control-group, and pre-, post-, and follow-up assessments (e.g., Parent et al., 2019). These available web-based programs are self-administered (Gelatt et al., 2010) and do not provide background support from health professionals (e.g., psychologist; Gelatt et al., 2010). Besides that, these programs also do not address the many unrealistic expectations so common in stepfamilies that contribute to high levels of marital and parental dysfunction (Higginbotham and Adler-Baeder, 2008a; Higginbotham and Agee, 2013). Furthermore, to the authors’ knowledge, no intervention tools (traditional or web-based) have yet been developed for Portuguese stepfamilies.

### Aims

To fill the gaps in the literature, our protocol intends to evaluate the efficacy and feasibility of a new web-based psychoeducational intervention (*GSteps*). The protocol outlines a comparison with a non-intervention control condition in a sample of Portuguese speaking adults in stepfamilies (parents and stepparents). The protocol offers options to examine changes in *stepparenting and co-parenting attitudes, remarriage beliefs, dyadic marital adjustment, marital social skills* and *family function.*

## Methods and analysis

### Study design

This study protocol is a two-arm double-blind prospective RCT comparing a web-based psychoeducational intervention to a waiting control condition among adults in stepfamilies (*N* = 112). The proposed intervention consists of a three-module (Figure 1) interactive Game that lasts a minimum of 30 and a maximum 60 min and can be played over the course of 1 month in computer. Modules are sequential and focus on the romantic relationship, co-parenting and step-parenting. Assessments are made before (*T_0_*) and 1 month after the intervention (*T_1_*). The experimental group (EG) has a second follow-up after 2 months (*T_2_*). The control group (CG) is on a waiting list until completion of *T_1_*, and then gets access to the intervention. Intervention and measurements are carried out online. The protocol uses the learning app H5P and *Limesurvey* survey design tool integrated into Moodle e-learning management system. The use of H5P interactive teaching aids to solve problems has been studied in literature as an important tool for educational context (Wang et al., 2016; Sinnayah et al., 2021). Figure 2 displays the study schedule of enrollment, interventions and assessments. This RCT will follow the SPIRIT guidelines (Chan et al., 2013a, 2013b) and the CONSORT statement (Moher et al., 2010; Schulz et al., 2010).

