**Figure 4 fig4:**
[figure not shown]
Branching scenario from Scene 10 of Module 2-“Stepparenting.”

*Wait-list*. After replying to the baseline questionnaire (*T_0_*), participants assigned to this condition receive a message informing that they are on the waiting list to participate on the course. The wait-list CG is also notified that they will be receiving further instructions in 1 month, and that access to the course is be possible after replying to a second assessment (*T_1_*).

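### T1 and T2 are stated inconsistently, so the only randomised comparison could be taken at different times from randomisation in the two arms

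*Protocol article*

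**What the plan says.** All places are in the protocol article.

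- **Abstract, Methods/design:** after baseline, assessments come "after the intervention (*T_1_*) and 1-month follow-up (*T_2". T1 therefore follows the intervention, and T2 is a 1-month follow-up.
- **Study design, T1:** one assessment is before the intervention, the other "and 1 month after the intervention".
- **Study design, T2:** "The experimental group (EG) has a second follow-up after 2 months". The point from which the 2 months run is not given.
- **Study design, playing time:** the Game "can be played over the course of 1 month in computer". The GSteps development section also gives 1 month as the allotted time.
- **Wait-list paragraph (GSteps development):** CG members are told after T0 that they "will be receiving further instructions in 1 month, and that access to the course is be possible after replying to a second assessment". CG T1 is thus tied to the calendar, about 1 month after T0.
- **Instruments and measures:** efficacy is judged on measures taken at T0 and T1; T2 is for the EG only.
- **Statistical analysis section:** the main test is a group-by-time interaction. T1 is labelled there as the post-test and as the assessment following the intervention.

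**The concern.** On the plain wording, the point 1 month after the intervention is T2 in the abstract and T1 in Study design. The two arms are also anchored to different events: EG T1 to the intervention, which may take anything up to a month, and CG T1 to the date of T0.

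This matters because T0 to T1 is the only randomised contrast. If the arms are measured at different times from randomisation, spontaneous change over time, the spacing between questionnaires and the opportunity to drop out differ by arm together with treatment. Once the CG has answered T1 it receives the Game, and T2 is collected in the EG alone, so no later data could separate the two.

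The meaning of the result is also unsettled. T1 could describe an immediate effect or an effect 1 month on, and T2 could describe durability over different spans.

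**Working it through.** The plan gives no figure to reproduce here; the check is timeline arithmetic in months from T0.

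**Inputs**

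- *m*, the time at which an EG member finishes the Game: 0 to 1 month (Study design; GSteps development).
- CG T1 = 1 (Wait-list paragraph).
- Assumption: the EG has access immediately. Recruitment and randomization describes automatic allocation and messaging once T0 is complete, so T0, randomisation and start of access are treated as one date.

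**Formulas for EG T1** (gap = EG T1 − CG T1)

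- Reading A, Study design taken literally: EG T1 = *m* + 1, gap = *m*.
- Reading B, abstract with T1 at individual completion: EG T1 = *m*, gap = *m* − 1.
- Reading C, months counted from the start of access: EG T1 = 1, gap = 0.

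| Finish (*m*) | A: EG T1 | A: gap | B: EG T1 | B: gap | C: EG T1 | C: gap |
|---|---|---|---|---|---|---|
| 0 | 1.00 | 0 | 0 | −1.00 | 1 | 0 |
| 0.25 | 1.25 | +0.25 | 0.25 | −0.75 | 1 | 0 |
| 0.5 | 1.50 | +0.50 | 0.50 | −0.50 | 1 | 0 |
| 1 | 2.00 | +1.00 | 1.00 | 0 | 1 | 0 |

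Under A the EG is measured 0 to 1 month later than the CG; under B, 0 to 1 month earlier. If the abstract's T1 is instead taken when the 1-month playing window closes, the gap is 0, as in C.

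**T2 (EG only)**

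- Reading B: one month after completion, *m* + 1, or 1 to 2 months from T0. This is the same time point as T1 under A.
- Reading C: month 2, which is one month after T1. This fits both the abstract's 1-month follow-up and the 2 months in Study design.
- Reading A: it depends on the missing origin. From T0, T2 is at month 2, which coincides with T1 for someone who finishes on the last day (1 + 1 = 2). From the end of play it is *m* + 2, or 2 to 3 months.

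Reading C is the only one of the three that fits the abstract, the Wait-list paragraph, the analysis section and the figures in Study design together. It requires the Study design phrase to mean after the *start* of the intervention, which is not what it says.

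**The case against.** The strongest reply is that Reading C is probably what was meant. The Game has an allotted month. T1 at its close is naturally a post-test, the CG is called at the same time, and T2 one month later satisfies both descriptions. In addition, Study design refers to Figure 2 for the schedule of assessments. That figure is not shown in the text reviewed, so whatever it fixes cannot be counted as missing. This stands, and it makes the timing gap conditional. It does not remove the conflict in wording between the abstract and Study design, which would need correcting even if the figure is clear.

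A reader might infer three stronger things that the article does not support:

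- **That EG T1 could fall anywhere from days after randomisation to about 2 months.** No single definition gives that range. It joins the early end of Reading B to the late end of Reading A.
- **That EG members who never finish the Game have no T1 date.** This would follow only if T1 were triggered by individual completion, and no section says so. The analysis is by intention to treat, and Strengths and limitations promises e-mail reminders for the later assessments without limiting them to finishers.
- **That the arms differ in retest exposure.** By T1 both have answered the same number of assessments; only the spacing could differ.

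The largest gaps also need extreme cases: a last-day finisher under A or an immediate finisher under B. The article gives nothing from which to estimate how far the outcomes drift in a month, so a calendar gap cannot be turned into a bias.

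**Conclusion.** The inconsistency is real and sits in the current text. Its consequence is conditional. EG T1 falls 0 to 1 month after CG T1 under the literal Study design text, 0 to 1 month before it under the abstract with T1 at completion, and at the same time if months run from the start of access. At its extreme the gap equals the whole CG interval of about 1 month.

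Under the first two readings the randomised contrast *could* mix intervention effect with elapsed time, irreparably so. It would go too far to conclude that the arms will be measured at different times or that the comparison is confounded, because one coherent reading gives no gap and the schedule figure may confirm it.

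These results assume immediate access after randomisation and CG response when called at 1 month. The point still merits correction: it concerns the date of the only randomised comparison, and the article states that date in conflicting ways.

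**What to change.** Reconcile the abstract, Study design, the Wait-list paragraph and the statistical analysis section, and check Figure 2 against them:

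1. State T1 as one fixed interval from randomisation, with a window, identical in both arms.
2. Send the T1 invitation to every EG member on that date, whether or not the Game was finished.
3. State T2 for the EG from the same origin.
4. Use these definitions wherever T1 and T2 appear.

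The cost is a change of wording and the date setting of the automatic e-mail. No assessments are added.

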**Figure 1 fig1:**
[figure not shown]
The three Game modules of *Gsteps* − Module 1: onjugality; Module 2: Stepparentimg; Module 3: Co-parenting.

**Figure 2 fig2:**
[figure not shown]
Study schedule of enrollment, intervention and assessments.

### Instruments and measures

A sociodemographic questionnaire will be used at *T_0_* to describe the sample and compare groups. Primary and secondary outcome measures administered at *T_0_* and *T_1_* will assess intervention efficacy and changes in marital quality, remarriage beliefs, co-parenting and stepparenting attitudes, and family functioning. Stability of these changes is assessed at *T_2_* for those in the EG. Specific outcomes related to the quality of the intervention and perceptions of intervention benefits will be accessed after the intervention for participants in the experimental condition group.

#### Sociodemographic questionnaire

Socio-demographic data is obtained through a questionnaire that included gender, date of birth, educational attainment, professional status, number of (step) children and financial and economic situation. The questionnaire will also include questions regarding respondent’s relationship history (pre-remarital status, type of divorce (when applicable), time spent between the previous and current relationships and length of the remarried relationship).

